#### Secondary outcome measures

Secondary outcome measures will be assessed at 3, 6 and 12 months post-randomisation (unless otherwise indicated) and include:Difference in the proportion of participants who have returned to at least 80% of pre-injury working hours at 3 and 6 monthsDifference in mean number and percentage of pre-injury hours returned to work, days of sickness absenceDifference in the proportion of participants intending to return to work/education, intending to retire, with type of work/education changesDifference in time to return to work/education (measured using bespoke questions)Difference in mean psychological wellbeing scores (Patient Health Questionnaire-9 (PHQ-9) [38], Generalised Anxiety Disorder Assessment-7 (GAD-7) [39], 6-item Impact of Events Scale (IES-6) [50])Difference in mean work self-efficacy scores (2 items from the Workability Index [51]) at 12 monthsDifference in mean financial impact of injury score (3 items from the Financial Chronic Stress Scale [52])Difference in mean purpose in life score (4-item Purpose in Life Test – Short Form [53]) at 12 months

#### Health economics

Difference in mean health-related quality of life (EQ-5D-5L [54]) at 3, 6 and 12 monthsDifference in resource implications and cost-effectiveness (bespoke questions on health and social care resource use) at 3, 6 and 12 monthsCost-effectiveness and cost utility per participant at 12 months

### Participant timeline {13}

Following admission to an MTC, patients will be screened for eligibility, their informed consent will be obtained and baseline assessments will be completed prior to randomisation. OTs will contact participants within two working days of randomisation to organise the initial assessment session, which should ideally take place within 2 weeks of randomisation. The intervention will continue up to 12 months post-randomisation, depending on participant need. The duration of usual care will vary between MTCs based on service provision at each site. Participants will complete follow-up questionnaires at 3, 6 and 12 months post-randomisation. A participant timeline (Fig. 1) and flow chart (Fig. 2) have been completed in accordance with SPIRIT Guidelines [34].

**Fig. 1 Fig1:**
[figure not shown]
Timeline of screening, recruitment, randomisation, interventions and assessments

**Fig. 2 Fig2:**
[figure not shown]
CONSORT flow diagram

### Sample size {14}

The planned sample size for the study is 722 recruited participants equally distributed across usual care and ROWTATE VR intervention plus usual care. This will provide at least 90% power, at the 5% significance level, to detect a between-group 15% absolute difference in return to work rates, with an expected 60% return to work rate in the control arm, allowing for up to 30% loss to follow-up at 12 months and design effect up to 1.221. The design effect appropriately inflates the required sample size for a individually randomised controlled trial to account for clustering resulting from therapist-delivered interventions in both study arms. The design effect assumes an intra-cluster coefficient (ICC) less than or equal to 0.03 (80, 81); an expected cluster size (number of participants seen per therapist) of ~ 11 participants (~ 8 analysable participants) with four therapists per site in the intervention arm across eight sites, and a coefficient of variation in cluster size less than or equal to 0.25 (i.e. cluster sizes ranging 3–14 participants). The remaining therapists across the eight sites will provide usual care.

This sample size is sufficient with 93% power to detect a moderate 0.3 effect size between randomised groups in health-related quality of life measured by the EQ5D using the same assumptions as the primary outcome calculation. This is based on a standard deviation (SD) of 0.248 in those who had not returned to work and 0.176 in those who had returned to work obtained from unpublished data from our Impact of Injuries Study [55]. The minimal important difference for the EQ-5D has been estimated to be 0.074 [56].

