## Methods: assignment of interventions

### Allocation

#### Sequence generation {16a)

Individual participants will be randomly assigned to usual care or ROWTATE plus usual care in a 1:1 allocation ratio. Allocation will use a 24-h computer-generated minimisation programme incorporating a random element, with minimisation factors: Site, age (16-30, 31-45, 46-60, 61-69), sex (male, female), time since injury (0 to 4 weeks, 5–8 weeks, 9–12 weeks) and ISS (9–15, > 15).

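### The EQ-5D power statement pairs an effect size of 0.3 with 93% power, but 0.30 gives about 86% and 93% needs about 0.34

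*Protocol article*

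**What the plan says.** All of this is in the protocol article, Sample size {14}, except the allocation ratio.

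- Size: "The planned sample size for the study is 722 recruited participants equally distributed across usual care and ROWTATE VR intervention plus usual care". Sequence generation {16a} confirms 1:1 allocation.
- Primary outcome: "This will provide at least 90% power, at the 5% significance level, to detect a between-group 15% absolute difference in return to work rates". The control-arm rate is put at 60%. Attrition of up to 30% and a clustering inflation of up to 1.221 are built in.
- EQ-5D: "This sample size is sufficient with 93% power to detect a moderate 0.3 effect size between randomised groups in health-related quality of life". As to the inputs, the remainder of that sentence describes this outcome as "measured by the EQ5D using the same assumptions as the primary outcome calculation".
- The EQ-5D calculation is said to rest on SDs of 0.248 in people who had not returned to work and 0.176 in people who had, from unpublished data. The next sentence adds: "The minimal important difference for the EQ-5D has been estimated to be 0.074".

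The section does not say which raw EQ-5D difference was targeted, which SD standardised it, or what the effect size is to a second decimal.

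**The concern.** Every input that the EQ-5D sentence needs is printed, so its power can be checked directly, and 0.3 with 93% does not come out. The gap is about 7 percentage points: at exactly 0.30 the type II error would be about 14%, not the 7% that 93% power implies. EQ-5D also supplies the QALYs for the economic evaluation. A reader of a null EQ-5D comparison who took the printed pair at face value would overstate how firmly a 0.3 SD difference had been ruled out.

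**Working it through.** **Inputs** (Sample size {14}): 722 recruited in equal arms, 30% loss, design effect 1.221, 5% significance. Sidedness is not printed; I use two-sided, which the primary calculation supports.

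**1. Effective number per arm.** 722 × 0.70 / 2 = 252.7 analysable. 252.7 / 1.221 = 207.0 effective.

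**2. Reproduce the primary power.** For 60% against 75%, the mean proportion is 0.675. The SE under the null is √(2 × 0.675 × 0.325 / 207.0) = 0.0460. Under the alternative it is √((0.60 × 0.40 + 0.75 × 0.25) / 207.0) = 0.0454. Power = Φ((0.15 − 1.96 × 0.0460) / 0.0454) = Φ(1.31) = 90.6%. This agrees with the stated minimum of 90%, so the shared assumptions are read correctly.

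**3. EQ-5D at d = 0.30.** The noncentrality is d × √(n/2) = 0.30 × √103.5 = 3.05. Power = Φ(3.05 − 1.96) = Φ(1.09) = 86.3% by the normal approximation, and 86.1% by the noncentral t.

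**4. Effect size that gives 93%.** d = (1.960 + 1.476) × √(2/207.0) = 0.338 (0.339 by the noncentral t). Keeping d = 0.30 and asking for 93% would need about 263 effective per arm: 2 × 263 × 1.221 / 0.70 ≈ 918 recruited.

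**5. Where 93% could come from**

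| Route | d | Power | Consistent with the text? |
|---|---|---|---|
| 0.074 / √((0.248² + 0.176²)/2) = 0.074 / 0.215 | 0.344 | 93.7% | Same N, loss, design effect and alpha; rounds to 0.3; not stated |
| 0.074 / 0.248 | 0.298 | about 86% | Same N, loss, design effect and alpha; rounds to 0.3; not stated |
| d = 0.30 without the design effect (252.7 per arm) | 0.30 | 92% | Contrary to using the primary assumptions |
| d = 0.30, one-sided 5% | 0.30 | 92% | Contrary to the two-sided primary calculation |

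The first route is the only one listed that comes close to 93% without changing a shared assumption.

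**6. Sensitivity of the first route to the SD.** The two SDs describe returners and non-returners, whereas each arm mixes both. With a proportion p of returners and a gap g in mean EQ-5D between the two groups, the arm variance is p × 0.176² + (1 − p) × 0.248² + p(1 − p)g². The gap is not in the document, so g is an assumption. Taking p = 0.60 and 0.75 from the primary calculation, averaging the two arm variances, and targeting 0.074 with 207.0 per arm:

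| Assumed g | SD | d | Power |
|---|---|---|---|
| 0 | 0.202 | 0.366 | 96% |
| 0.16 | 0.215 | 0.344 | 93.7% |
| 0.18 | 0.219 | 0.338 | 93.0% |
| 0.20 | 0.222 | 0.333 | 92% |
| 0.30 | 0.245 | 0.302 | 86% |

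**The case against.** The best defence is that 93% is a sound figure beside a rounded effect size. A power calculation for a purely standardised effect needs no SD. Quoting two SDs and then a minimal important difference therefore suggests that a raw difference of 0.074 was the target. On that reading d = 0.344, the power is 93.7% with loss and clustering both applied, and 0.344 is 0.3 to one decimal.

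Most of this stands. A reader might infer from step 3 that 93% cannot follow from the trial's own figures, or that the true type II error is twice what is stated. The document does not support either. The 0.344 route uses only printed numbers and changes no shared assumption, and the 14% holds only if 0.3 means 0.300. Nor does combining the SDs of returners and non-returners show 93% to be wrong: the root-mean-square SD equals a proper arm-level SD at an assumed gap near 0.16, and 93% lies inside the 86% to 96% range.

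The defence does not rescue the sentence as printed. It names 0.3 as the effect to be detected and never calls 0.074 the target, and the section's figures also yield 0.298 with about 86%. One-decimal rounding that moves power by 7 to 8 points is too coarse beside a power quoted to the nearest percent.

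The consequence is also limited. EQ-5D is not the primary outcome. Results are to be reported with confidence intervals (Statistical methods {20a}), and cost-effectiveness will be judged by net monetary benefit and acceptability curves (Health economic analysis), not by a powered EQ-5D test.

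**Conclusion.** The statement is wrong as written, and the correction is minor. Under 722 recruited, 30% loss, design effect 1.221 and two-sided 5%, 0.30 goes with about 86% power and 93% goes with about 0.34. The likeliest explanation is 0.344 rounded to 0.3, but that is an inference. If 0.074 was the target, its power depends on a gap between returners and non-returners that the document does not give: about 96% down to 86% for an assumed gap of 0 to 0.30. The primary power reproduces at 90.6%, and the sample size stands.

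**What to change.** In Sample size {14}, state the raw EQ-5D difference targeted, the SD used to standardise it and the effect size to two decimals. Then print the pair that matches the calculation actually done:

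- about 0.34 SD (a difference of 0.074) with 93% power; or
- 0.30 SD with 86% power.

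The authors must check which input they used. Simply replacing 93% with 86% would introduce an error if 0.344 was the input. If 0.074 is the target, also say that the SDs of returners and non-returners were combined, and that the arm-level SD depends on the mean difference between those groups. Report that difference from the unpublished data, or give the power range.

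The cost is a sentence or two of text. If 0.30 was the input, the stated EQ-5D power becomes less favourable. No participant number or analysis changes.

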#### Recruitment (15)

Potential participants will be identified at MTCs using a range of methods including bespoke trauma patient databases containing all patients with moderately severe or major trauma defined as an ISS > 8. Daily lists of inpatient trauma patients and daily trauma rounds, supplemented by knowledge of trauma/rehabilitation coordinators, ward occupational therapists and trauma case managers will assist in identifying appropriate patients.

Potential participants will be approached by their usual care team to introduce the study and assess eligibility. Those who are eligible will be given the participant information sheet (PIS) and an expression of interest form (EOI). If patients are discharged before they are approached, they will be phoned by the usual care team to discuss the study. They will be posted a study invitation, PIS and EOI form as well as receive an email if they have access to email. Those unable to be contacted via phone will receive a posted study invitation, PIS and EOI form. Those expressing interest will be contacted by the usual care team or a researcher to assess eligibility. An anonymised screening log will be used to monitor potentially eligible participants up to 12 weeks after admission to the MTC and returned monthly to the Clinical Trials Research Unit (CTRU) to aid identification of recruitment issues. Recruitment can take place either face-to-face or remotely via video call or phone. The target recruitment was at least six participants per MTC per month (after the first 3 months of recruitment) over a 20-month recruitment period, with staggered start dates for sites. Due to slower than anticipated recruitment, the recruitment target was subsequently amended to 32 participants per month across all eight MTCs and the recruitment period extended to 30 months, with an anticipated recruitment end date of 31/3/2024. Regular single-site and multisite recruitment meetings will be held to identify and respond to recruitment challenges.

All sites will participate in an internal pilot, which will assess the recruitment rate 10 months after the first two sites commence recruitment, and the retention rate 10 months later. The progression criteria are shown in Table 1. If any criteria are graded as amber, or another issue is identified which could affect successful trial completion, a rescue plan will be developed outlining steps to be taken to improve recruitment, and/or follow-up (as appropriate). This will be approved by the Trial Steering Committee (TSC) before submission to the National Institute for Health and Care Research (NIHR). If only red progression criteria are achieved, the Trial Management Group (TMG), TSC and funder will determine if the trial should be stopped.

**Table 1 Tab1:** Progression criteria for the internal pilot

• Green (go): mean of more than 6 participants recruited per month per site; At least 80% of participants complete the primary outcome
• Amber (modify): mean of 4–6 participants recruited per month per site; 60–79% of participants complete the primary outcome
• Red (stop): mean of less than 4 participants per month per site; Less than 60% of participants complete the primary outcome

## Methods: assignment of interventions

### Allocation

#### Sequence generation {16a)

Individual participants will be randomly assigned to usual care or ROWTATE plus usual care in a 1:1 allocation ratio. Allocation will use a 24-h computer-generated minimisation programme incorporating a random element, with minimisation factors: Site, age (16-30, 31-45, 46-60, 61-69), sex (male, female), time since injury (0 to 4 weeks, 5–8 weeks, 9–12 weeks) and ISS (9–15, > 15).

#### Concealment mechanism {16b}

The online, central randomisation service will ensure allocation concealment, as allocation information will only be released after the patient has been consented and recruited into the trial, and after all baseline measurements have been completed.

#### Implementation {16c}

Randomisation will be requested by the staff member responsible for recruitment from the online, central randomisation service. An automated email will be sent from the randomisation service to the staff member responsible for recruitment, the site PI and the site’s intervention OTs confirming randomisation and the participant’s allocation. Research staff will inform the participant’s GP of study participation via letter. OTs will keep a record of all recruited participants to ensure they do not treat usual care participants. The Clinical Trials Research Unit (The CTRU) will inform participants via letter of their allocation with details of subsequent actions (e.g. follow-up assessments, OT contact).

### Blinding

#### Who will be blinded? {17a}

Participants and personnel delivering the intervention will not be blind to allocation group. To minimise the risk of detection bias, baseline data will be collected prior to participant randomisation. Researchers from other participating sites (not the recruitment site) who are blind to the allocation group will conduct priming calls prior to each follow-up time point to inform participants of upcoming questionnaires and to collect primary outcome data. If the researcher administering priming calls at the site becomes unblinded, they will be asked to inform CTRU as soon as possible and priming calls will be assigned to another researcher at the site.

#### Procedure for unblinding {17b}

Neither participants, the site researchers nor intervention delivery teams will be blinded to treatment allocation; therefore, there is no requirement for emergency unblinding procedures in this study.

## Methods: data collection and management

### Plans for assessment and collection of outcomes {18a}

Baseline assessments (Table 2) will be collected by clinical staff/researchers at site via face-to-face/telephone/video conferencing in hospital or following discharge as close as possible and prior to randomisation (within 12 weeks of admission to MTC).

**Table 2 Tab2:** Baseline assessments

Assessment	Type	Method of completion
Participant demographics	Questionnaire booklet	Researcher/self-completion
Contact details	CRF	Researcher
Injury details	CRF	Researcher
Montreal Cognitive Assessment (MoCA)	CRF	Researcher
Work/education status	Questionnaire booklet	Researcher/self-completion
Health-related quality of life (EuroQol EQ-5D-5L)	Questionnaire booklet	Researcher/self-completion
Patient Health Questionnaire (PHQ-9)	Questionnaire booklet	Researcher/self-completion
Generalised Anxiety Disorder Assessment (GAD-7)	Questionnaire booklet	Researcher/self-completion
Impact of events scale (15 items)	Questionnaire booklet	Researcher/self-completion
World Health Organisation Disability Assessment Schedule 2.0 (12 items)	Questionnaire booklet	Researcher/self-completion
Recovery expectations	Questionnaire booklet	Researcher/self-completion
Financial Chronic Stress Scale (3 items)	Questionnaire booklet	Researcher/self-completion

*CRF* case report form

Follow-up assessments for primary, secondary and health economic outcomes will be measured by participant self-reported questionnaires at 3, 6 and 12 months post-randomisation (Table 3). This will be done either by telephone, postal or online completion using internet-based software (REDCap) depending on participant preference.

**Table 3 Tab3:** Follow-up assessments

Assessment	Type	Method of completion	3 months	6 months	12 months
Discharge Information (including final ISS score)	CRF	Researcher	Quarterly		
Work/Education status	Questionnaire booklet	Researcher / Self-completion	X	X	X
Health-Related Quality of Life (EuroQol EQ-5D-5L)	Questionnaire booklet	Researcher / Self-completion	X	X	X
Patient Health Questionnaire (PHQ-9)	Questionnaire booklet	Researcher / Self-completion	X	X	X
Generalised Anxiety Disorder Assessment (GAD-7)	Questionnaire booklet	Researcher / Self-completion	X	X	X
Impact of Events Scale (6 item scale)	Questionnaire booklet	Researcher / Self-completion	X	X	X
Work Ability Index (WAI item 1 (workability scale) WAI item 2 (physical and mental demands)	Questionnaire booklet	Researcher / Self-completion			X
Financial Chronic Stress Scale (3 item scale)	Questionnaire booklet	Researcher / Self-completion	X	X	X
Purpose in life test—short form scale (4 items)	Questionnaire booklet	Researcher / Self-completion			X
Health and Social Care Resource Use (inpatient and outpatient hospital visits, primary and community care use, medication, aids and adaptations, informal care)	Questionnaire booklet	Researcher / Self-completion	X	X	X
Intervention Resource Use (intervention session content and additional activity forms recording therapist’s direct time and indirect time (time travelling to/from treatment appointments and administrative time)	CRF	Occupational therapists and clinical psychologists	Throughout intervention period		
Safety Reporting (workplace accidents requiring medical attention, workplace accidents involving equipment or adaptations to work environment, injuries received, healthcare used)	Questionnaire booklet	Researcher / Self-completion	X (only if RTW)	X (only if RTW)	X (only if RTW)

*RTW* return to work

#### Assessment instruments

The primary outcome of return to work for at least 80% of pre-injury hours will be captured using the following three questions:Are you currently in work/ voluntary work/education in any capacity (including a phased return)?Which of these statements currently applies to you?I am workingI am doing voluntary workI am on a Government programme aimed at finding a jobI am studying on a courseI am on a Government programme aimed at finding a courseHow many hours are you currently working or in education for each week?

Priming calls will be made to participants prior to administration of follow-up questionnaires and primary outcome data will also be collected, where possible at priming calls using the questions above. For those not contactable by priming calls, two-way SMS messaging will be sent asking participants to confirm work/education status (the primary outcome).

Secondary and health economic outcomes will be measured by a combination of bespoke questions and standardised tools. Bespoke questions will assess work/education intentions, time to return to work/education, retirement, sickness absence; and health and social care resource use. Outcomes measured using standardised tools include:Health-Related Quality of Life using with the EuroQol EQ-5D-5L which measures self-reported health outcomes regarding mobility, self-care, usual activities, pain/discomfort and anxiety/depression [54]. It has been recommended by guidelines for use in comprehensive injury populations including injury of moderate severity and major trauma [57]Psychological wellbeing using:PHQ-9 which is designed to screen for depression [38] in a variety of medical settings and is highly sensitive and specific [58]. It has been found to be a valid tool amongst acutely injured trauma survivors [59] and have high sensitivity, specificity and test–retest reliability in people with traumatic brain injury [60].GAD-7 which is used to screen for generalised anxiety disorders in a range of medical settings [39] and is highly sensitive and specific [61] and shows high internal consistency amongst people with TBI [62].IES-6 to measure post-traumatic distress symptoms. It has been shown to have high internal consistency, and high sensitivity and specificity with a cut-off of a mean score of 1.75 for a diagnoses of PTSD based on the Clinician Administered PTSD Scale [50]. It has also been shown to predict psychological distress in burn survivors at 6 months and 2 years post -injury [63].Work self-efficacy using Work Ability Index which measures participants’ self-reported estimation of ability to do their work with respect to work demands, health and mental resources [51]. Items 1 (workability scale) and 2 (separate questions on physical and mental demands) will be used. Item 1 has been shown to predict sustainable RTW in construction workers with musculoskeletal conditions [64].Financial impact of injury using Financial Chronic Stress Scale (3 item scale) which measures satisfaction with financial situation, difficulty meeting monthly bill payments and monthly finances [52].Purpose in Life Test – Short Form which assesses a person’s perceived meaning and purpose in life. The scale contains 4 items measuring presence of goals, goal completion and meaning in life. Responses are on a Likert scale ranging from 1–7 with a total score ranging from 4 to 28. Higher scores on this scale are indicative of greater reported purpose in life. It has been shown to have acceptable reliability [53].

Research staff will receive training to ensure standardised completion of study-specific assessments.

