The intervention will ideally commence within 2 weeks of randomisation. Content, dose, intensity and duration (up to 12 months post-randomisation) will be individually tailored based on participant’s needs, preferences and specific employment contexts. The intervention will include:Assessing the impact of the injury on the participant, family and the participant’s role as a workerSetting and reviewing vocational goalsEducating participants, employers and families about the effects of the injury and its impact on work and find acceptable strategies to lessen that impactMonitoring and adjusting the participant’s post-injury life and work goalsPreparing participants for work by establishing structured routines with gradually increased activity levels and opportunity to practice work skillsLiaising with relevant stakeholders such as employers, employment advisors (e.g. occupational health), solicitors and the healthcare team to advise about the effects of the injury and to plan and monitor a phased return to workRoutine monitoring of mood and emotional issues, via routine use of questionnaires, observation and responses during clinical sessions, by the OT and, if needed, the CP

The need for CP involvement will be determined by the OT screening for mental health problems using validated measures (Patient Health Questionaire-9 (PHQ-9) [38], Generalised Anxiety Disorder Assessment-7 (GAD-7) [39], 15-item Impact of Events Scale (IES-15) [40], Whooley depression screening questions [41], Patient Health Questionnaire-Panic Disorder (PHQ-PD) [42]) at the initial intervention assessment and again at 6 months post-randomisation. Following a stepped care approach [43], participants scoring in the “moderate” range on psychological measures will be monitored by the OT for 1 month and if no improvement will be discussed with or referred to the CP. Participants scoring in the “severe” range on psychological measures will be referred to the CP for psychological assessment and support as needed. OTs can also discuss or refer participants to the CP who do not score in the moderate or severe range on psychological measures if they consider this clinically necessary.

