### Outcomes {12}

#### Primary outcome measure

The difference between the two randomised groups in the proportion of participants who have returned to work at 12 month post-randomisation. This is defined as returning to employment or self-employment, voluntary work or full-time education and working at ≥ 80% of pre-injury working hours. This outcome measure arose from a focus group of major trauma survivors comprising a diverse range of injury types and causes (e.g. road traffic, sports, workplace injuries and falls), including multiple trauma and also traumatic brain injury. It included both professional and “blue collar” occupations pre-injury, some had made a successful return to work and some had not. The group discussed what constituted successful return to work, including the number of hours that would constitute a successful return to work/education and our primary outcome was developed based on this. Return to at least 80% of pre-injury working hours has also been used in previous research with major trauma patients to define complete or nearly complete return to work [48, 49]. This will be measured using bespoke questions as described under data collection methods below.

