## Statistical methods

### Statistical methods for primary and secondary outcomes {20a}

A detailed statistical analysis plan will be finalised and agreed by the research team prior to analysis.

A single final analysis is planned after the trial is closed to recruitment and follow-up and when the full database has been cleaned and locked. Analyses will be completed by the CTRU statisticians using SAS version 9.4 [66].

The primary analysis will compare the proportions of participants in work/education for ≥ 80% of the their pre-injury hours 12 months post-randomisation between arms, using a two-level mixed effects logistic regression model, accounting for therapist-level clustering (in both arms) as random effects. The model will adjust for treatment allocation, data informing stratification factors (site, age, sex, time since injury and ISS; included as continuous covariates where applicable) and other relevant known predictors of the outcome as fixed effects. If a participant is unable to report their working status, e.g. if they are dead, this will be taken as they have not returned to work. Otherwise missing data will be assumed missing at random and multiple imputation will be used in primary analyses.

Analysis of secondary outcomes at 3, 6 and 12 months will use the same approach as the analysis for the primary outcome measure with the relevant model for the type of outcome variable using multi-level linear (adjusted for baseline where appropriate), logistic or Cox regression as appropriate.

Results will be expressed as point estimates (mean difference, odds ratios, hazard ratios), together with standard errors, 95% confidence intervals and *p* values. Unadjusted and adjusted ICCs will also be reported.

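### The SMS back-up is described as confirming work/education status, labelled the primary outcome, without the weekly hours that the 80% threshold needs

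*Protocol article*

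**What the plan says.** All references are to the protocol article.

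- **Primary outcome measure** (Outcomes {12}): success means being in employment, self-employment, voluntary work or full-time education and "working at ≥ 80% of pre-injury working hours" at 12 months. The primary analysis in section {20a} uses the same threshold.
- **Assessment instruments**: the outcome "will be captured using the following three questions". The first asks "Are you currently in work/ voluntary work/education in any capacity (including a phased return"), the second asks the type of activity, and the third asks current weekly hours.
- **Same section, priming calls**: primary outcome data are collected "where possible at priming calls using the questions above", that is, with all three items.
- **Same section, SMS**: "For those not contactable by priming calls", "two-way SMS messaging will be sent asking participants to confirm work/education status (the primary outcome"). Hours are not mentioned.
- **Retention {18b}**: non-responders to the questionnaire get two reminders, the second a short form limited to the primary outcome and the EQ-5D-5L.
- **Table 1**: the pilot's retention criterion is the share of participants who complete the primary outcome (green at 80% or more, red below 60%).
- **Statistical methods {20a}**: participants who cannot report working status, for example because of death, are counted as not returned. "Otherwise missing data will be assumed missing at random and multiple imputation will be used in primary analyses".

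**The concern.** The SMS sentence attaches the name of the primary outcome to a looser quantity. Being in work in any capacity is necessary for success but not sufficient, because someone on a phased return answers yes to the status question while working below the threshold.

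The two possible replies therefore carry unequal information. Not in work fixes the outcome as a failure. In work leaves it open. If SMS is the only source for a participant, an in-work reply must either be scored on status, which overstates success, or be set aside, which removes likely successes while keeping failures. The same label also leaves it open whether a status-only reply counts as a completed primary outcome for the pilot's retention criterion.

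This differs from an analysis rule that can wait for the SAP. If no route collects hours for a participant, later analysis can only classify or impute them.

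**Working it through.** **The plan's own figure.** For 60% versus 75%, 90% power and two-sided 5% (sidedness assumed), the pooled formula without continuity correction gives 203 per arm. Then 2 × 203 × 1.221 / 0.70 = 708, close to the stated 722. In reverse, 361 × 0.70 / 1.221 = 207 effective participants per arm, with power 90.6%. The sample size is sound and does not depend on this point.

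**What each reply determines.**

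| SMS reply | Outcome at the 80% threshold |
|---|---|
| Not in work | Not returned (determined) |
| In work, hours given | Determined, given pre-injury hours |
| In work, no hours | Not determined |

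**Illustration on assumed values.** Let s be the share of outcomes that rest on a status-only SMS, and q the share of true non-successes who are in work below 80% of hours. The document gives neither. I take s from 5% to 30% and q from 20% to 40%, and assume that SMS-only participants have the same true rates as the rest of their arm.

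*Route A: in-work replies scored as successes.* Observed rate = p + s·q·(1 − p).

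- With q equal in both arms the difference is 15 × (1 − s·q) points. At s = 5%, q = 20% it is 14.85 points (power 90.2%). At s = 20%, q = 40% it is 13.8 points (86.9%). At s = 30%, q = 40% it is 13.2 points (84.7%).
- With q unequal and s = 20%: q = 20% control and 40% intervention gives 77.0% − 61.6% = 15.4 points (92.7%). The reverse gives 76.0% − 63.2% = 12.8 points (81.0%). At s = 30% the reverse gives 76.5% − 64.8% = 11.7 points (74.5%).
- With no true effect (60% in both arms), s = 20%, and q = 20% in one arm and 40% in the other, the spurious difference is 0.20 × 0.40 × (0.40 − 0.20) = 1.6 points, in favour of whichever arm has the larger q.

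*Route B: in-work replies set to missing while not-in-work replies are kept, with status not used in the imputation.* Let w = p + q·(1 − p) be the share in work. Observed rate = p(1 − s) / (1 − s·w). Imputation by arm alone reproduces this rate.

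- At s = 20%, q = 20%: control w = 0.68, 0.48 / 0.864 = 55.6%; intervention w = 0.80, 0.60 / 0.84 = 71.4%. The difference is 15.9 points.
- At s = 20%, q = 40%: control w = 0.76, 0.48 / 0.848 = 56.6%; intervention w = 0.85, 0.60 / 0.83 = 72.3%. The difference is 15.7 points.

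Both arms' rates fall, because a control participant known to be in work has a success probability of 0.60 / 0.68 = 88.2% (q = 20%) but is imputed at 55.6%. Using work status in the imputation removes this error if, within arm, SMS-only participants in work resemble other participants in work.

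**The case against.** The strongest reply is that the phrase is shorthand. The SMS script is not reproduced, and Tables 2 and 3 use work/education status as the name of a questionnaire section. That is the only Table 3 row that could hold the hours question. A two-way exchange can carry more than one item. This reading is possible, so it cannot be said as fact that the SMS asks for nothing else. But the preceding sentence expressly applies the three questions to calls, and the SMS sentence does not, so a site following the text has no instruction to ask hours.

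Secondly, other routes exist. SMS and priming calls precede the questionnaire, which everyone is then asked to complete, with two reminders to non-responders. This stands, and limits the problem to participants who answer the SMS and nothing else.

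Thirdly, coding rules and imputation models belong in the SAP. That is fair for the rules. It does not cover whether hours are asked.

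A reader might also infer two stronger things:

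- *Phased returners are counted as successes.* No section scores a status-only reply as success, and the endpoint is stated consistently at 80% elsewhere.
- *The error favours the intervention, because its therapists liaise with employers* "to advise about the effects of the injury and to plan and monitor a phased return" *to work.* That describes a process. It does not say which arm has more people below 80% of hours at 12 months. If the in-work share were equal in both arms, more sub-threshold working with the intervention would imply lower true success there. With q equal in both arms, misclassification shrinks a true benefit.

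**Conclusion.** The point holds in a limited form. As written, the SMS route equates status with an hours-based endpoint. For participants whose only reply is by SMS, in work does not determine the primary outcome while not in work does. Those replies would be misclassified or selectively missing.

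The direction of bias is open and its size cannot be determined from the document, because neither the SMS-only share nor the share working below 80% of hours is given. The assumed ranges above suggest a modest effect in most scenarios, reaching a few points only when many outcomes rest on SMS alone. They are illustrations, and no single value should be cited as the expected bias. The planned sample size is unaffected. The change is worth making because it is cheap and because hours that were never collected cannot be recovered.

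**What to change.** 1. State that the SMS also asks current weekly hours, using the third question under Assessment instruments. If it already does, correct the sentence to say so.
2. For a reply that still lacks hours where no questionnaire or reminder supplies them: code not in work as not returned. Treat in work as missing for the 80% outcome and impute it with work status as an auxiliary variable. Do not count it as a success.
3. Do not count an in-work reply without hours as a completed primary outcome for the retention criterion in Table 1.

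The cost is one more SMS question and one derivation rule, and slightly fewer SMS replies will count as complete. With recruitment expected to end on 31/3/2024, 12-month follow-up runs to about the end of March 2025. The added question therefore helps only contacts still to come when it is adopted. The coding rule covers replies already received.
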